## Abstract

**Background:**

Endoscopic mucosal resection (EMR) is currently the most used technique for resection of large distal colorectal polyps. However, in large lesions EMR can often only be performed in a piecemeal fashion resulting in relatively low radical (R0)-resection rates and high recurrence rates. Endoscopic submucosal dissection (ESD) is a newer procedure that is more difficult resulting in a longer procedural time, but is promising due to the high en-bloc resection rates and the very low recurrence rates. We aim to evaluate the (cost-)effectiveness of ESD against EMR on both short (i.e. 6 months) and long-term (i.e. 36 months). We hypothesize that in the short-run ESD is more time consuming resulting in higher healthcare costs, but is (cost-) effective on the long-term due to lower patients burden, a higher number of R0-resections and lower recurrence rates with less need for repeated procedures.

**Methods:**

This is a multicenter randomized clinical trial in patients with a non-pedunculated polyp larger than 20 mm in the rectum, sigmoid, or descending colon suspected to be an adenoma by means of endoscopic assessment. Primary endpoint is recurrence rate at follow-up colonoscopy at 6 months. Secondary endpoints are R0-resection rate, perceived burden and quality of life, healthcare resources utilization and costs, surgical referral rate, complication rate and recurrence rate at 36 months. Quality-adjusted-life-year (QALY) will be estimated taking an area under the curve approach and using EQ-5D-indexes. Healthcare costs will be calculated by multiplying used healthcare services with unit prices. The cost-effectiveness of ESD against EMR will be expressed as incremental cost-effectiveness ratios (ICER) showing additional costs per recurrence free patient and as ICER showing additional costs per QALY.

**Discussion:**

If this trial confirms ESD to be favorable on the long-term, the burden of extra colonoscopies and repeated procedures can be prevented for future patients.

**Trial registration:**

NCT02657044 (Clinicaltrials.gov), registered January 8, 2016.

## Background

Resection of colorectal adenomas has shown to lower the mortality rate due to colorectal cancer with 60 % [1]. Especially large adenomas maintain a high risk of progression to invasive cancer, underlining the importance of adequate resection [2]. Endoscopic resection of large adenomas has been proven to be feasible and safe, with less morbidity, mortality and costs compared to surgical resection [3]. Endoscopic resection of non-pedunculated adenomas is most often performed using the ‘lift-and-cut’ endoscopic mucosal resection (EMR) technique [4]. However, in adenomas larger than 2 cm in size EMR can often only be performed in a piecemeal fashion (pEMR) due to the limited size of the snare, difficulty to position the endoscope, and often extension of the polyp over one or multiple folds [5, 6]. Although safe, piecemeal resection lowers the reliability of assessing the dysplasia free resection margins (R0 resection) at histology. This is also reflected by the relative high recurrence rate at follow-up colonoscopy after EMR ranging between 12-16 %, and even increasing up to 30 % in non-pedunculated polyps exceeding 40 mm in size [7, 8].

For this reason endoscopic submucosal dissection (ESD) was developed in Japan, a technique that enables to achieve en-bloc resection even in large polyps [9]. Several retrospective observational studies compared EMR and ESD. A recent meta-analysis pooled the results yielding a total of 2299 lesions [10]. Although studies were biased by baseline differences with special regard to tumor location and polyp size due to lack of a randomized design, results are promising. Rates of en bloc resection and radical resection were much higher, and the rate of recurrence was much lower in the ESD-group (91.7, 80.3 and 0.9 % respectively) than in the EMR-group (46.7, 42.3 and 12.2 % respectively). This benefit comes at the expense of an about three-fold longer procedure time and more complications (perforation rate 5.7 % versus 1.4 %). However, this safety profile may be favorable in the distal colon, given the lower risk for complications as compared to proximally located polyps [11]. We hypothesize that the prolonged procedure time will initially result in higher healthcare costs, but that this time-investment will earn itself back on the long-term due a higher number of R0-resections and lower recurrence rates with less need for repeated procedures. If indeed ESD proves to be (cost-)effective on the long-term, burden of extra colonoscopies and repeated procedures can be prevented for patients in the future. It is important to address this gap in the current knowledge, especially now that screening programs have been widely introduced and the detection of large adenomas will further increase.

Therefore, the aim of this randomized clinical trial is to evaluate the effectiveness and cost-effectiveness of ESD against EMR on both short (i.e. 6 months) and long-term (i.e. 36 months) for large (>20 mm) distal non-pedunculated adenomas.

## Methods

This randomized clinical trial will randomize between ESD and EMR in patients with large distal non-pedunculated colorectal adenomas. Seventeen Dutch hospitals will participate, including three academic and fourteen non-academic hospitals. The flowchart of the design of the MATILDA-trial is displayed in Fig. 1.

**Fig. 1 Fig1:**
[figure not shown]
Flowchart of the study design of the MATILDA-trial

### Study population

The eligible study population consists of adult patients with a non-pedunculated polyp larger than 20 mm in the rectum, sigmoid, or descending colon found during screening, surveillance or diagnostic colonoscopy

Inclusion criteria:non-pedunculated polyp larger than 20 mm in the rectum, sigmoid or descending colon found during colonoscopyindication for endoscopic treatment≥18 years oldWritten informed consent

Exclusion criteria:suspicion of malignancy, as determined by endoscopic findings (invasive Kudo pit pattern, Hiroshima type C) [12, 13] or proven malignancy at biopsyprior endoscopic resection attemptpresence of synchronous distal advanced carcinoma that requires surgical resectionthe risk exceeds the benefit of endoscopic treatment, such as in patients with an extremely poor general condition or a very short life expectancythe inability to provide informed consent

### Study setting

The endoscopists participating in this trial are selected based on predefined criteria. With the knowledge that the operational difficulty of colon ESD is very high, a minimum prior number of procedures was defined in order to avoid that results will be biased by a learning curve. Based on the literature, 25 colorectal ESD-procedures is considered to be required to achieve expert experience [14–16]. Previous esophageal and stomach ESD experience alone will not be enough to ensure colorectal ESD expertise, as colorectal ESD is known to be technically more difficult than upper gastro-intestinal ESD due to the more challenging anatomical characteristics of the colon (thin wall, folds, peristalsis, angulated positions, and fecal fluid) [17]. This study will therefore only allow endoscopists that have performed >25 colorectal ESD procedures in the past three years to treat patients randomized to the ESD arm. In centers without ESD-experienced endoscopists, patients will be referred to an ESD-expert center when randomized to the ESD-arm. Patients randomized to the EMR arm will be treated by endoscopists which have extensive experience with EMR, defined as >500 prior EMR’s of which >50 in colorectal adenomas larger than 20 mm.

### Recruitment and randomization

Initial recruitment of patients will be performed by the local coordinating investigator of the participating center. When a polyp is found at index colonoscopy that fulfills the inclusion criteria, exclusion criteria will be checked. In presence of exclusion criteria, this will be registered in the screening log. In absence of exclusion criteria, the local coordinating investigator will provide oral and written information on the study to the patient. Patients will have as much time as they like to think about participation and will have the chance to ask any questions on the study. Thereafter the informed consent form is signed. In case of non-participation, this will be recorded in the screening log (see Fig. 1). Independent computer-based randomization will be performed (Castor Electronic Data Capture (EDC), CIWIT b.v.) in a 1:1 ratio. Randomization will be stratified by the size of the polyp (20-30 mm, 31-40 mm, >40 mm), localization (rectum, sigmoid, descending colon) and center using block sizes of five per block. Due to the nature of the treatment, neither patients nor endoscopists participating in this study will be blinded.

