With regard to the outcome measures, we chose to evaluate the primary outcome measure recurrence rate after a duration of 6 months. From literature, it is known that about 76 % of recurrences after EMR occur after 3 months, increasing to 96 % after 6 months [35]. Thus, 6 months seems the moment we are able to catch the vast majority of the recurrences. However, studies that looked at long-term recurrence rates also found that recurrence can occur up to 36 months after EMR [35–37]. Therefore, we feel a second outcome measure for long-term follow-up is obligatory for this trial. R0-resection was chosen as secondary outcome measure as this might be an important factor to decide for the frequency and interval of follow-up colonoscopies in future patients. If our assumption is correct that a R0-resection does not show recurrence at long-term follow-up, this will offer an argument to prolong the interval and frequency of follow-up colonoscopies after ESD with R0-resection. Last, we decided only to apply a healthcare payer perspective when conducting the cost-effectiveness analysis. Argument is that most of the patients will be above 65 years and thus retired, absence from work and/or lower efficiency while at work (i.e. productivity losses) will be rare. Adding an additional questionnaire for investing potential work losses from unpaid work were considered too burdensome, and not pay off for the increased risk of early termination.

In the development of the study design, sources of bias were attempted to be minimized. Stratified randomization will be performed in order to prevent confounding. Moreover, in order to pre-empt confounding due to differences in operator experience between the groups, we decided only to allow endoscopists with sufficient prior experience to participate in this trial. Threshold values for participation were determined based on previous published literature and are defined in the study protocol [14–16]. Due to the nature of the treatment, neither patients nor endoscopists participating in this study will be blinded. In order to avoid information bias in the endoscopists’ evaluation of recurrence, the study protocol mandates endoscopists to take biopsies of the post-polypectomy scar. In this way, an objective evaluation is guaranteed.

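### The single published block size of five, within strata that include centre, lets a recruiter in this open trial know a few next allocations before enrolment; the effect is modest and cheap to reduce

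*Protocol article*

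**What the plan says.** All the elements are in the protocol article, mostly in one section.

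- **Strata and blocks** (Recruitment and randomization): "Randomization will be stratified by the size of the polyp (20-30 mm, 31-40 mm, >40 mm), localization (rectum, sigmoid, descending colon) and center", with one block length, "and center using block sizes of five per block". The stated ratio is 1:1.
- **Centres** (Methods): "Seventeen Dutch hospitals will participate".
- **Who recruits** (Recruitment and randomization): "Initial recruitment of patients will be performed by the local coordinating investigator of the participating center". The same person checks exclusions and informs the patient.
- **Blinding** (Recruitment and randomization): "neither patients nor endoscopists participating in this study will be blinded".
- **Protection of the list** (Recruitment and randomization): "Independent computer-based randomization will be performed", in Castor EDC, described after the consent step.
- **Visibility of allocation** (Study setting): centres without an experienced ESD endoscopist send their ESD patients to another hospital.
- **Discretion over entry** (Study population): one exclusion rests on judging that endoscopic treatment would do more harm than good.
- **Bias control** (Discussion): "Stratified randomization will be performed in order to prevent confounding". The paragraph also covers operator experience and scar biopsies, but not predictability of allocation.

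**The concern.** A central computer hides the allocation list. It cannot hide what past allocations reveal when the block length is fixed and known. Once one arm has had its maximum in a block of five, the rest of that block is determined. Before that point the odds already move away from 50:50. Because centre is a stratum, the relevant history builds up at one hospital, in front of the person who recruits there.

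A recruiter who expects a given arm could delay, discourage or exclude a particular patient. That selection happens before randomisation, so an intention-to-treat analysis cannot undo it. In an open trial, concealment is the main protection at enrolment. The planning rates in Sample size calculation (2% and 12%) imply few events: 99 × 0.02 + 99 × 0.12 ≈ 14 recurrences among 198 evaluable patients. A handful of steered enrolments could therefore be noticeable. The documents give no basis for estimating the resulting bias in the recurrence difference, and none is claimed here.

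**Working it through.** **Inputs from the document.** 212 patients; 17 centres; 3 size classes; 3 locations; fixed block of five; 1:1 ratio. The plan gives no figure for predictability, so there is none to reproduce.

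**Inputs assumed.** The document gives neither the split within a block of five nor the recruitment mix. Two block compositions are examined: 3:2 and 2:3 equally likely (mixed), and 3:2 always in the same direction (constant). Recruitment runs from even across all cells to skewed (three centres recruit 65%; locations 60/30/10; sizes 40/30/30). The guesser is assumed to know the possible block sizes and all earlier allocations in the stratum.

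**Step 1: one full block of five.**

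*Mixed.* The 4th allocation is certain if the first three were all to one arm: 1/C(5,3) = 1/10. The 5th is certain if the first four split 3:1, which means the last place belongs to the minority arm: 2/5.
- Certain: (0 + 0 + 0 + 0.1 + 0.4)/5 = 10%.
- Best guess correct: (0.5 + 0.6 + 0.6 + 0.7 + 0.7)/5 = 62%.

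*Constant 3:2.* The 3rd is certain if both minority places are used in the first two: 1/C(5,2) = 1/10. The 4th is certain in 0.4 of blocks, and the 5th always.
- Certain: (0 + 0 + 0.1 + 0.4 + 1)/5 = 30%.
- Best guess correct: (0.6 + 0.6 + 0.7 + 0.7 + 1.0)/5 = 72%.

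**Step 2: how many blocks fill.** There are 17 × 3 × 3 = 153 strata, so 212/153 ≈ 1.4 patients per stratum on average. Most blocks stop early, and the full-block figures overstate the trial's exposure.

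**Step 3: trial-scale simulation.** Patients are assigned at random to the 153 strata and blocks are drawn within each. The conditional probability of the next allocation is computed exactly. An allocation counts as certain when that probability is 0 or 1. The best-guess rate is the mean of max(p, 1 − p).

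| Scheme | Certain, even to skewed | Best guess correct |
|---|---|---|
| Five, mixed | 0.8–4.5% | 55–58% |
| Five, constant 3:2 | 3.5–14.2% | 62–66% |
| Random 2, 4, 6 | 0.2–1.5% | 60–63% |
| Random 4, 6 | 0.4–3.2% | 57–61% |
| Random 4, 6, 8 | 0.0–1.1% | 56–60% |

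For the varying schemes the guesser knows the menu of sizes but must infer where each block begins, so these rows are pessimistic if the menu is withheld.

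**Step 4: in patients.** Mixed fives: 0.008 × 212 ≈ 2 to 0.045 × 212 ≈ 10 certain allocations. Sizes 4, 6 and 8: 0 to 0.011 × 212 ≈ 2.

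**Step 5: which composition is plausible.** Constant 3:2 blocks, if all filled, would give 212 × 3/5 ≈ 127 against 85. The plan states 1:1 and 106 per arm. Mixed blocks are the reading that fits, so the first row is the main result.

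**The case against.** **The effect is small.** This stands. On the reading that fits the 1:1 ratio, at most about ten allocations are certain, and that upper end needs a recruitment concentration that the document does not report.

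**A reader might infer that allocation is largely predictable.** The text does not support this. The higher range needs every block to lean the same way, against the stated ratio. A calculation with centre as the only stratum would give larger figures, but it describes a design that this trial does not use.

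**A reader might infer that recruiters know the block size and track each cell.** The document says neither. The size is in the published article and allocations are visible, so both are possible, but they remain assumptions.

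**A reader might infer that large polyps could be steered to one arm.** This goes too far. Any prediction is made within one size, location and centre cell, and allocation is blocked on those factors. Beyond unfinished blocks, selection cannot shift the balance across the size or location classes. What remains is difficulty within a cell, including size within the open-ended class above 40 mm.

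**There are safeguards.** Exclusions and refusals go into a screening log. An independent monitor checks the entry criteria after a centre's first five patients, with later visits only if needed. The malignancy exclusion is tied to named endoscopic classifications or to biopsy. These give a partial trail. They do not prevent a recruiter from anticipating the next arm, and a discouraged patient looks like an ordinary refusal.

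**Varying blocks do not clearly lower guessing.** This also stands. Against mixed fives, sizes 2, 4 and 6 raise the best-guess rate to 60–63%, and 4, 6 and 8 do not lower it. The improvement is in certain allocations.

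**Conclusion.** The point holds in a limited form. The stated rule combines one published block length, centre as a stratum, open treatment and local recruitment, so a few allocations can be known before enrolment. Under mixed blocks this is about 1 to 4.5% of patients, with best guesses 55 to 58% correct. About 4 to 14% and 62 to 66% would apply only under constant 3:2 blocks. The result rests on an assumed recruitment mix, an assumed block composition, and a recruiter who knows the size and follows the cell history.

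This is an avoidable weakness that should be corrected, not evidence that selection occurred or that the comparison is invalid. The sample size of 198 evaluable and 212 randomised patients is unaffected.

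**What to change.** For all new blocks, replace the fixed block of five with randomly varying even block sizes that leave out size 2, for example 4, 6 and 8. Tell sites only that permuted blocks of varying size are used. Keep the sizes in a restricted document until recruitment ends. The withholding matters as much as the variation, because the size of five is already public.

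Even sizes also fit the 1:1 ratio within each block, which five cannot do.

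**Cost.** A change to the randomisation settings and one sentence in the protocol, with no extra patients or procedures. The document does not describe how Castor EDC is configured, so the effort there is assumed to be small. There are two downsides: larger blocks may leave slightly more imbalance where they stay unfinished, and average guessing is not reduced relative to mixed fives.

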### Outcome measures

A schedule of the study procedures with the outcome measures is presented in Table 1.

**Table 1 Tab1:**
[figure not shown]
Schedule of the study procedures

*COREFO* Colorectal Function Outcome, *CRC* colorectal cancer, *D* days, *EMR* endoscopic mucosal resection, *EQ-5D-5 L* EuroQol-5 dimensions-5 levels, *ESD* endoscopic submucosal dissection, *HCR* health care resources, *QoL* quality of life, *M* months, *W* weeks; * only performed when recurrence is found at the 6 month colonoscopy; ** only be performed when recurrence is found at the 6 and 12 month colonoscopy; *** only performed when recurrence is found at the 6 and 12 and 18 month colonoscopy

#### Primary outcome

Recurrence rate at follow-up colonoscopy after six months. This will be observed from resected residual disease or, if not present, from biopsies of the post-polypectomy scar [18].

#### Secondary outcomes

Radical (R0-)resection rate. This is defined as dysplasia free vertical and lateral resection margins at histology.Perceived burden and quality-of-life (QoL) among patients at 36 months. This will be assessed using questionnaires. A summary of the investigated domain and type of questions can be found in Table 2. In short, colorectal cancer anxiety is measured at baseline, 4 days and 4 weeks after ESD/EMR, and after the 6 and 36 months follow-up colonoscopy using an instrument originally designed and validated in breast cancer patients, and subsequently used to evaluate patients’ perception of colorectal cancer risk [19, 20]. Burden of the procedure will be measured on day 4 after ESD/EMR and after the 6 months follow-up colonoscopy using an instrument proven to be a reliable and valid assessment in prior studies [21–23]. Functional complaints will be measured at baseline, 4 weeks after ESD/EMR, and after the 36 months follow-up colonoscopy using the Colorectal Function Outcome (COREFO) instrument [24]. Quality-of-life will be measured at baseline, 4 days and 4 weeks after EMR/ESD, after the 6 months follow-up colonoscopy, 13 months after EMR/ESD, and after the 36 months follow-up colonoscopy using the EQ-5D-5L-instrument [25]. The EQ-5D, developed by the EuroQol group, will be used to calculate quality adjusted live years (QALYs) and consists of two parts, the EQ-5D descriptive system and the EQ visual analogue scale (EQ-VAS). The EQ-VAS records the participant’s self-reported health on a VAS from 0 (labeled “worst imaginable health state”) to 100 (labeled “best imaginable health state”). The EQ-5D descriptive system consists of five domains (i.e. mobility, self-care, usual activities, pain/discomfort and anxiety/depression) and five functioning levels (i.e. no problems, slight problems, moderate problems, severe problems or unable to function). The questionnaires will be send digital to the participating patients by Castor EDC (CIWIT b.v.). A reminder will be send when participants don’t respond. Patients who prefer to complete the forms on paper will receive the questionnaires by mail.

**Table 2 Tab2:** Patients’ perceived burden and quality of life assessment

	Item	N	Method of measurement	Scale
Patients’ perception of treatment	Burden of the procedure	3	Verbal measure	5-point scale
	Burden afterwards	3	Verbal measure	5-point scale
	Overall perception	1	VAS	1-10
Patients’ perception of CRC risk	CRC Risk Perception	3	1. VAS	1. 1-100
			2. Verbal measure	2. 7-point scale
			3. Comparative measure	3. 3-point scale
	CRC Worry	2	Verbal measure	7-point scale
Colorectal Functional Outcome	Incontinence	9	Frequency measure	5-point scale
	Social impact	9	Frequency measure	5-point scale
	Frequency	2	Frequency measure	5-point scale
	Stool-related aspects	3	Frequency measure	5-point scale
	Need for medication	3	Frequency measure	5-point scale
EQ-5D-5 L instrument	Quality of life	5	Verbal measure	5-point scale
	Overall health status	1	VAS	0-100

Abbreviations: *CRC* colorectal cancer, *N* number of questions per item, *VAS* Visual Analogue ScaleHealth resources utilizations and costs at 36 months. Data on healthcare utilization will be gathered in the electronical case record form for instruments used, time needed to perform the procedure, admission to the ward and/or intensive care, length of hospital stay, (repeated) treatment or (prolonged) hospital stay for complications, used anesthesia and anesthesia staff, material and time needed for repeated treatment or (prolonged) hospital stay for recurrence and surgical referral. These data will be used to calculate healthcare costs.Surgical referral rate at 36 months. This is defined as the total number of patients that are referred for surgical management.Long-term recurrence rate at follow-up colonoscopy after 36 months. This will be observed from resected residual disease or, if not present, from biopsies of the post-polypectomy scar.Complication rate within 30 days after treatment. Intraprocedural perforation is defined as the condition in which the abdominal cavity is visible from the colorectal lumen during the procedure because of mural tissue defects, that requires (1) (prolonged) admission or (2) surgery. Intraprocedural bleeding is defined as bleeding that occurs during the procedure that is not controlled by electrocoagulation and/or hemoclipping, and that requires (1) transfusion or (2) termination of the endoscopic resection. Postprocedural bleeding is defined as bleeding within 30 days after the procedure resulting in (1) new presentation at the hospital, (2) hospital admission, or (3) repeated colonoscopy to obtain hemostasis. Postprocedural perforation is defined as perforation within 30 days after the procedure that is detected after completing of the procedure during which perforation did not occur, diagnosed by abdominal pain with focal guarding and a rise in C-reactive protein and/or fever (T >38.5 C) in combination with free air in the peritoneal cavity at abdominal CT-scan. Postprocedural serositis is defined as abdominal pain with focal guarding and a rise in C-reactive protein and/or fever (T >38.5 C) within 30 days after the procedure, but without signs of perforation (free air at abdominal CT-scan) and in the absence of another infection focus (urinary, pulmonary etcetera).

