## Discussion

This will be the first randomized clinical trial comparing ESD and EMR for large distal non-pedunculated polyps. This study will not only provide information on the effectiveness and safety of both treatment strategies, but will also give insights in perceived patient burden, quality of life, the costs and cost-effectiveness of both treatments. Given that all patients in this study will be followed for a total duration of 36 months, we will be able to evaluate both short-term (i.e. 6 months) as well as long-term (i.e. 36-months) outcome measures.

We decided to include only patients with distal polyps in this trial. Not only because we expect that the risk profile for ESD will be more favorable in the rectum compared to the right colon, but also because most experience with ESD in the Netherlands currently exists with distal lesions [33]. We decided to include only non-malignant neoplasia in this trial, as we think it is unethical to randomize patients with suspected T1 CRC to the EMR arm. Given that EMR in polyps exceeding 20 mm in size is most often performed in a piecemeal fashion, inclusion of patients with suspected T1 CRCs in this trial would undoubtedly result in unnecessary referral of low risk T1 CRCs for surgery due to positive resection margins [34].

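### Both perforation definitions depend on the abdominal or peritoneal cavity, so read literally they do not count a full-thickness defect into extraperitoneal tissue as a perforation, although the rectum is an eligible site

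*Protocol article*

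**What the plan says.** The definitions are in the protocol article, Secondary outcomes, under the complication rate within 30 days.

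- **Intraprocedural perforation** is "the condition in which the abdominal cavity is visible from the colorectal lumen during the procedure because of mural tissue defects", with the added condition "that requires (1) (prolonged) admission or (2) surgery".
- **Postprocedural perforation** needs abdominal pain with guarding and an inflammatory response, "in combination with free air in the peritoneal cavity at abdominal CT-scan".
- **Postprocedural serositis** needs the same clinical picture, "but without signs of perforation (free air at abdominal CT-scan"), and no other focus of infection.

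Study population admits a "non-pedunculated polyp larger than 20 mm in the rectum, sigmoid, or descending colon". Recruitment and randomization makes location (rectum, sigmoid, descending colon) a stratification factor. Background gives pooled perforation rates of 5.7% for ESD and 1.4% for EMR and presents this as part of the price of ESD's better resection results. Data analysis compares the complication rate between arms with a stratified test for binary outcomes.

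**The concern.** Part of the rectum lies below the peritoneum. This is general anatomy and is not stated in the document. A full-thickness defect confined to that part opens into perirectal tissue: the abdominal cavity does not come into view, and any escaped air can remain outside the peritoneal cavity. Such an event would meet neither perforation definition, even if it led to admission or surgery.

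Perforation is the specific harm that the protocol quotes against ESD, and few events are expected. If some cannot be classified as perforations, the trial could report a smaller absolute excess with ESD than actually occurred. Endoscopists are not blinded, so deciding informally whether an extraperitoneal defect counts would add avoidable judgement to a safety comparison.

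**Working it through.** **1. The definitions side by side.** Take a full-thickness rectal defect confined to extraperitoneal tissue.

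| Category | Anatomical or CT criterion | Is it met? |
|---|---|---|
| Intraprocedural perforation | abdominal cavity seen from the lumen | No |
| Postprocedural perforation | free air in the peritoneal cavity on CT | No |
| Serositis, no air on CT | no free air on CT | Yes, if the clinical criteria are met |
| Serositis, extraperitoneal air only | no free air on CT, site not stated | Unclear |

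The last row turns on the wording. The perforation definition places the air in the peritoneal cavity; the serositis exclusion gives no location. If the exclusion means any free air, a delayed case with only extraperitoneal air belongs to neither category. If it is shorthand for the sign just defined, the case counts as serositis. On neither reading is it a perforation.

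**2. Other places that might pick it up.** Trial interventions registers intraprocedural perforation but gives no wider definition. The list of resection-related AEs in Safety monitoring does not name postprocedural perforation. The SAE definition includes any other related event, but only above severity thresholds such as more than 10 days of admission, surgical intervention, ICU admission or death. None of these routes adds the event to the perforation count.

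**3. Illustrative size.** Inputs:

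- Patients per arm: 106 (Sample size calculation). The plan's figure can be reproduced. The unpooled normal formula for 12% versus 2%, with two-sided alpha 0.05 and 80% power, gives (1.960 + 0.842)² × (0.12×0.88 + 0.02×0.98) / 0.10² = 98.3, so 99 per arm and 198 in total. Then 198 × 1.07 = 211.9, or 212, which is 106 per arm. The point does not depend on this calculation.
- Perforation rates: 5.7% ESD and 1.4% EMR (Background).
- Share f of perforations that the definitions cannot count: **not in the document**. It is assumed here at 10%, 25% and 50%, equal in both arms.

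Counted events per arm = 106 × rate × (1 − f). Counted risk difference = (5.7 − 1.4) × (1 − f) percentage points.

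| f | ESD events | EMR events | Excess events | Risk difference (points) |
|---|---|---|---|---|
| 0 | 6.04 | 1.48 | 4.56 | 4.30 |
| 10% | 5.44 | 1.34 | 4.10 | 3.87 |
| 25% | 4.53 | 1.11 | 3.42 | 3.23 |
| 50% | 3.02 | 0.74 | 2.28 | 2.15 |

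The ratio stays at 5.7 / 1.4 = 4.1 throughout, because f is the same in both arms. Only the absolute difference shrinks.

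**The case against.** Several counter-arguments have force.

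- **The events do not vanish.** A contained case without air on CT can count as serositis and so stay in the overall complication rate. Severe cases can be reported as SAEs. Overnight admission is registered with its reason, and patients referred for surgery enter the surgical referral rate. This stands: it would be wrong to infer that such harm is lost from the trial. None of these routes, however, labels the event a perforation.
- **The serositis exclusion can be read as shorthand.** It follows directly after the perforation definition, so its free air may mean peritoneal air. This is a fair reading, and it makes the classification ambiguous rather than certainly missing.
- **The abdominal cavity may be taken to include the retroperitoneal space.** The claim is therefore not established for the back wall of the descending colon during the procedure. The case rests mainly on the extraperitoneal rectum.
- **The magnitude is soft.** The 5.7% and 1.4% are pooled from observational studies that Background itself calls biased by tumour location. How those studies defined perforation is not given, and Background suggests a lower complication risk distally. The intraprocedural definition also requires admission or surgery, so not all of the 6.0 and 1.5 events need be countable at any site. The table illustrates the direction and order of size only.

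A reader might also infer that the definition builds in a favourable rectal result, since the Discussion says "we expect that the risk profile for ESD will be more favorable in the rectum compared to the right colon". The document does not support that. The sentence explains why only distal polyps are enrolled. The right colon is not an eligible site, so the trial cannot produce that contrast.

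**Conclusion.** The point holds as a defect in the definitions of a secondary safety outcome. Taken literally, a full-thickness defect confined to extraperitoneal tissue is not counted as a perforation, and a delayed case with only extraperitoneal air has an uncertain classification. The perforation component **can** be undercounted and the absolute ESD-EMR difference understated. That a material undercount **will** occur is not shown, because the document gives no extraperitoneal share.

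Under the assumed 10-50% share, about 0.5 to 2.3 of an expected excess of 4.6 events would go uncounted. This rests on the pooled rates applying here and on equal shares in both arms; unequal shares would alter the ratio as well. The primary outcome and sample size are unaffected. The change should be made, but it does not threaten the main conclusion.

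**What to change.** For outcome classification only, with no change to how patients are managed:

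- **Intraprocedural perforation:** any full-thickness defect of the bowel wall seen during the procedure, whatever tissue or space lies beyond it. Keep the existing admission-or-surgery condition.
- **Postprocedural perforation:** extraluminal air on CT at any site (intra-, retro- or extraperitoneal). Keep the existing clinical and timing criteria.
- **Serositis:** use that same air criterion as the exclusion, so that the site of air no longer leaves a delayed case between the two categories.

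The cost is reworded definitions and matching eCRF fields, with no extra procedure. The downside is a slightly higher reported perforation rate and less direct comparability with studies that use the narrower definition. Recording the site of the defect or air would still allow the narrower count to be reported alongside.
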